### Criteria for discontinuing or modifying allocated interventions {11b}

Following randomization, peer counsellors will attempt to reach participants via telephone, text, and email (as necessary). Participants who do not respond after 8–10 attempts to establish contact will no longer receive treatment but will remain in the study. If any response is provided to attempted contact, peer counsellors will continue to reach out to schedule remote-counselling sessions, unless the participant expresses a desire to withdraw from the study or they reach the end of pregnancy. Participants will also no longer receive treatment if they do not complete the intervention before the end of pregnancy. If acute suicidality is indicated, either through the study questionnaires or in weekly remote-counselling sessions, the participant will no longer receive treatment and the clinical team will provide a referral to the appropriate care resources using the established referral pathway.

### Strategies to improve adherence to interventions {11c}

Peer counsellors will schedule weekly remote-counselling sessions in accordance with the participants’ availability and will remind participants of upcoming sessions about 24 h before the session or as decided with the participant. Sections of the self-administered workbook will be assigned for each session and participants will be reminded of the assigned sections. In the case that a participant has not completed the assigned materials before the session, the peer counsellor will guide the participant through the workbook content during the session time. In each session, peer counsellors will inquire as to the amount of assigned materials completed before session and any barriers to completing the BA materials. To ensure peer counsellor adherence to the protocol, peer counsellors will also attend a weekly 90-min clinical supervision with a member of the clinical team.

### Relevant concomitant care permitted or prohibited during the trial {11d}

Information on concomitant care will be gathered and tracked throughout the study to ensure that participants receiving care are evenly disbursed between groups. Inclusion will be restricted to individuals who meet the eligibility criteria and who do not have any current active treatment regimen for a diagnosed mental illness (e.g. medications and/or counselling), with the exception of participants who have been on a stable dose of anti-depressant medications (e.g. SSRIs) for 3 months or more. Participants receiving other psychological interventions for mental health problems, including depression and anxiety, will be excluded from the study.

### Provisions for post-trial care {30}

As participants in the control group will be offered standard of care, there will be no provision of the intervention post-trial. Standard of care materials, including a list of community resources, will be provided to both the treatment and control groups.

### Outcomes {12}

The primary outcome is gestational age at birth in days, measured using electronic health records, obtained for the P3 Cohort.

Secondary outcomes are:Change in symptoms of depression across T1 and T2 between the treatment and control groups, measured as overall score on the EPDS; and lower odds of scoring 13 or greater on the EPDS at T2, T3, and T4.Change in symptoms of anxiety across all timepoints (measured by the PROMIS – anxiety 7a-item short form self-report questionnaire [41])

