### Objectives {7}

The primary aim of this study is to conduct an RCT to determine the effectiveness of remote, peer-delivered behavioural activation (BA) therapy, plus ongoing informal peer-support intervention to individuals with AD in reducing preterm birth. We hypothesize that our intervention will be associated with an increase in gestational age at delivery compared to the standard of care.

The secondary aims of this trial are to determine whether the peer-administered intervention will be effective for treating AD prior to delivery, with persistence to 6 and 12 months postpartum, improving anxiety symptoms compared to controls.

We hypothesize that participants in the intervention group will have:Significantly greater reduction in depression symptoms from T1 to T2, and significantly lower odds of depression at T2, T3 and T4 compared to controlsSignificantly greater reduction in anxiety symptoms from T1 to T2, and significantly lower odds of depression at T2, T3 and T4 compared to controls

We will also qualitatively explore the lived experiences of peer counsellors in delivering the trial intervention. We hypothesize that experiences providing the intervention to peers will be perceived as positive and that peer counsellors may identify perceived benefits to their own mental well-being.

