### Eligibility criteria {10}

#### Inclusion and exclusion criteria

English-speaking pregnant participants over the age of 18, who complete the baseline P3 cohort questionnaire, and score >10 on the Edinburgh Postnatal Depression Scale (EPDS), who reside in the Calgary Health Region and are less than 27 weeks’ gestation (to enable completion of the intervention prior to delivery, and allow us to capture the vast majority of preterm deliveries) will be eligible for inclusion. Participants undergoing no current psychotherapy or pharmaceutical treatment, or who have been on a stable dose of anti-depressant medications (e.g. SSRIs) for 3 months or more and score 10 or more on the EPDS will be eligible. We will exclude anyone who has a lifetime diagnosis of severe psychiatric illness (bipolar disorder, schizophrenia, borderline personality disorder, other psychoses) and/or is engaged in an active treatment regimen for a diagnosed mental illness (counselling; non-SSRI medications) at trial intake.

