#### Screening and enrollment

After informed consent is obtained for the P3 cohort, including consent to be contacted for nested trials, participants meeting the study definition of AD will be identified by research assistants using weekly data queries. For the purposes of this study, AD is defined as a score of 10 or greater on the Edinburgh Postnatal Depression Scale (EPDS), which has been validated to measure major depressive disorder against diagnostic interviews (sensitivity 87.7%; specificity 90.9%) in pregnant individuals [34, 35]. All participants with AD will be invited to join this nested trial. Participants will be contacted by trained research assistants, provided with study information, and invited to enrol in the current study.

Written informed consent will be obtained in addition to the P3 cohort consent. Research assistants will screen participants further for eligibility and included participants will be randomized to receive the intervention or standard of care (control). Randomization will be conducted using computer-generated, block-randomization into an intervention group and a control group (receiving standard of care).

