## Statistical methods

### Statistical methods for primary and secondary outcomes {20a}

We anticipate that the block randomization will successfully eliminate confounding by covariates, but potential confounding variables will be measured on all questionnaires, and imbalance between intervention and control groups assessed prior to the final analysis. Any imbalance in confounding variables between the groups will be controlled for as appropriate, using cox proportional hazards or logistic regression modelling. Descriptive statistics will be calculated for all participant characteristics that have the potential to act as confounding variables on the primary association between the intervention and gestational age.

Time-to-event analysis will be used to assess change in our primary outcome of gestational age at delivery.

Logistic regression will be used to model the association between the intervention and categorical secondary outcome of depression (scoring 13 or greater on the EPDS), post-intervention, and 6 and 12 months postpartum. Secondary outcomes of difference in continuous scores on the EPDS (depression), PROMIS (anxiety), and parenting self-efficacy scales between intervention and control groups will be modelled using linear regression.

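### The binary depression outcome (EPDS 13 or greater) sits above the trial's own definition of antenatal depression (EPDS 10 or greater), so it cannot be read as remission of AD or as its persistence postpartum

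*Protocol article*

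**What the plan says.** Under Screening and enrollment, the protocol article fixes the condition under study: "For the purposes of this study, AD is defined as a score of 10 or greater on the Edinburgh Postnatal Depression Scale (EPDS". The sensitivity and specificity it quotes are attached to that definition.

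The Inclusion and exclusion criteria state the entry score in two ways: "score >10 on the Edinburgh Postnatal Depression Scale (EPDS" in general and, for untreated participants or those on stable antidepressants, "score 10 or more on the EPDS will be eligible". The Abstract uses the first form.

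Under Objectives {7}, a secondary aim is that the intervention be "effective for treating AD prior to delivery, with persistence to 6 and 12 months postpartum", and the matching hypothesis is lower odds of depression at T2, T3 and T4.

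Outcomes {12} gives two depression outcomes: change in the EPDS total between T1 and T2, and "lower odds of scoring 13 or greater on the EPDS at T2, T3, and T4". Statistical methods {20a} labels the second one the "categorical secondary outcome of depression (scoring 13 or greater on the EPDS), post-intervention, and 6 and 12 months postpartum" and models it by logistic regression. Continuous EPDS scores go to linear regression, with no visit named.

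The article gives no reason for moving from 10 to 13. It does not restrict the logistic analysis to those at 13 or more at T1, and it does not state adjustment for T1 EPDS.

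**The concern.** The same word describes two different states. At entry, depression means 10 or greater; as an outcome, it means 13 or greater. Participants between the two cut-offs are enrolled as cases and, by the outcome, are non-cases from the first visit. For them the outcome can only record worsening or its absence. For those who enter at 13 or more, crossing from 13 to 12 is scored as success although the trial would still class the participant as having AD.

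Interpretation is what is at stake. A reader who sees lower odds of depression at 6 and 12 months, next to an aim of treating AD with persistence, will take it to mean that AD resolved and stayed resolved. The outcome as defined does not measure that. The low absolute rates it would show in both arms would partly reflect who was enrolled.

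**Working it through.** **1. The plan's own figure.** Sample size {14} gives 214 participants for the EPDS comparison, inflated by 15%: 214 × 1.15 = 246.1, which reproduces the stated 246. That figure rests on the EPDS score, not on the binary outcome, for which no size or power is stated. With 107 per arm, 90% power and two-sided 5%, the implied standardised difference is (1.960 + 1.282) × √(2/107) = 0.443. The article gives no EPDS mean or SD.

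**2. The two definitions side by side.**

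| T1 score → later score | AD as defined (10 or greater) | Binary outcome (13 or greater) |
|---|---|---|
| 12 → 12 | present throughout | free of depression throughout |
| 13 → 12 | present throughout | success |
| 14 → 11 | present throughout | success |
| 12 → 7 | resolved | no change |
| 11 → 13 | present throughout | becomes a case |

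These rows need no distributional assumption. Entry at more than 10 narrows the affected band from 10–12 to 11–12 but does not remove it.

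**3. How many enter below 13 (assumption).** Write S(x) for the probability of scoring x or more in the screened cohort. The share is [S(10) − S(13)] / S(10), or [S(11) − S(13)] / S(11) if entry is more than 10.

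- Normal EPDS with S(10) = 0.15. The 15% is the AD prevalence in the Background, which the article does not tie to an EPDS cut-off.
  - SD 4: (0.150 − 0.0370)/0.150 = 75%. Entry above 10: (0.0991 − 0.0370)/0.0991 = 63%.
  - SD 6: (0.150 − 0.0622)/0.150 = 59%. Entry above 10: (0.1145 − 0.0622)/0.1145 = 46%.
- Normal EPDS with mean 5 to 8 and SD 4 to 5: 52% to 77% for entry at 10 or more, and 40% to 64% for entry above 10.

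Across both sets the range is roughly 40% to 77%.

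**4. Does power favour one cut-off?** Power = Φ(|p₁ − p₂| / √{[p₁(1 − p₁) + p₂(1 − p₂)]/107} − 1.96). The probabilities come from a normal score cut half a point below the threshold, and the intervention mean is 0.75 times the control mean (the plan's 25% difference).

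- SD fixed at 5:
  - Control mean 9: 0.242 v 0.125 at 13 gives 61%; 0.460 v 0.291 at 10 gives 74%.
  - Control mean 12: 93% and 94%. Here the standardised difference is 3/5 = 0.60, larger than the plan's 0.443.
- SD set so that the standardised difference stays at 0.443:
  - Control mean 9 (SD 5.08): 60% at 13, 72% at 10.
  - Control mean 12 (SD 6.77): 73% and 74%.
  - Control mean 13 (SD 7.33): 74% and 73%.

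A separate simulation used truncated baseline scores with T1–T2 correlation 0.5 or 0.7. A 1.5-point shift gave 41–67% power at 13 and 49–78% at 10; a 3-point shift gave 88–99% and 97–100%. The lower cut-off does better when follow-up means are low, and the advantage is gone by a control mean of 12 to 13.

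**The case against.** The strongest reply is that nothing here is biased. Allocation is randomised 1:1, so the T1 mix of scores is the same in both arms in expectation, and a difference in the odds of 13 or greater is a genuine treatment effect. That stands. A reader might infer that the outcome cannot show that AD was treated at all; the documents do not support that. The T1–T2 change in EPDS total also tests treatment directly: a fall from 12 to 7 counts there in full.

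That reply covers T2 but not persistence. Outcomes {12} limits the continuous measure to T1 and T2, and the linear regression in Statistical methods {20a} names no visit. Even a mean difference at T3 or T4 would not show that AD had remitted.

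A second reply is that a sensitive cut-off for entry and a stricter one for the outcome is a coherent pairing, that the article never uses the word remission, and that a rationale may be in the full protocol or the analysis plan. This also has weight, and it is why 13 or greater cannot be called wrong in itself. It does not remove the mismatch the article does contain: the aim is stated in terms of AD, AD is defined at 10, and the outcome is called depression without qualification.

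Finally, the share affected is assumption-driven and the power comparison is not decisive. Both are accepted.

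**Conclusion.** The point holds as one of definition and interpretation. The 13-or-greater outcome combines resolution among those who entered at 13 or more with prevented worsening among those who entered below it. It cannot be read as remission of AD as the trial defines it. Nor can it be read as persistence of remission at T3 and T4, where Outcomes {12} names no other EPDS outcome. This follows from the two cut-offs alone.

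The size does rest on assumptions: about 40% to 77% of entrants below 13 at T1, if EPDS is roughly normal with the means and SDs used above. The documents support neither a claim that the randomised contrast is invalid nor a claim that 10 or greater is the more powerful choice in general. Gestational age, the primary outcome, and the total of 246 are unaffected. This is a secondary-outcome matter, worth correcting because the correction is cheap.

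**What to change.** - In Objectives {7}, Outcomes {12} and Statistical methods {20a}, add EPDS 10 or greater (AD present, as defined for entry) as a binary outcome at T2, T3 and T4, and tie the claim of treating AD with persistence to it.
- Keep 13 or greater as a separately labelled outcome, not called simply depression. Adjust it for T1 EPDS or report it by T1 stratum (below 13 versus 13 or more), and state why 13 was chosen.
- Reconcile the more-than-10 and 10-or-more wordings in the Abstract, Inclusion and exclusion criteria, and Screening and enrollment, so that one definition serves both entry and the added outcome.

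The cost is wording plus one further secondary result to report and interpret. No new data are needed, since the EPDS is already administered at all four visits, and the sample size does not change.

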### Participant timeline {13}

The overall participant timeline is illustrated in Fig. 1.

Week 1 (T1): Participants of the P3 Cohort study will complete a baseline assessment during pregnancy (less than 27 weeks GA). Individuals who are eligible for this study will be identified and will be contacted by a member of the study team to be invited to participate. The study team member will outline the study protocols and obtain informed consent.

Week 2: Participants will be randomly assigned, using computer-generated block randomization, into the intervention group or the standard of care control group.

Weeks 3–6: Participants randomized to the intervention group will complete the BA counselling sessions with a peer counsellor via telephone, in addition to regular informal peer-support contact. Participants in the control group will continue to receive standard of care.

Week 8–10 (T2): At 34 to 36 weeks gestation, after the completion of the intervention, all participants will be invited to complete an electronic P3 Cohort questionnaire.

Post-due-date (up to 6 weeks postpartum): After childbirth, information about gestational age at delivery will be collected for the P3 cohort via linkage to the participant medical record. Participants will continue to have informal peer-support (social support, advice, information sharing) contact with peer counsellors via text and telephone, up to 6 weeks postpartum.

Five to 6 months postpartum (T3): All participants will be invited to complete an electronic questionnaire as part of their participation in the P3 Cohort.

Eleven to 12 months postpartum (T4): All participants will be invited to complete an electronic questionnaire as part of their participation in the P3 Cohort.

### Sample size {14}

This sample size of 246 participants (123 per group) is adequate to detect a minimally clinically significant change of 3 days in mean gestational age with 80% power at an α level of 5%. Based on a 2-sided *T*-test statistic and an α level of 5%, we will have 90% power to detect a minimally clinically significant difference of 25% in EPDS scores at intervention completion (T1), with a sample size of 214 participants [42]. We have inflated our estimated sample size by a factor of 15% (total *N*=246), to account for study attrition. A prior study demonstrated a reduction in EDPS scores up to 56% in a similar intervention during pregnancy [11]. A total of 60–75 peer counsellors will be recruited and trained to provide the intervention to between 1 and 3 participants through the course of the study. Additional peer counsellors will be recruited and trained as needed.

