
**Fig. 1 Fig1:**
[figure not shown]
SPIRIT schedule of enrolment, intervention, and assessments

Once the peer counsellors have obtained their competency approval, they will be paired with a single randomized participant and will establish contact with them to initiate and administer the intervention. The peer-delivered intervention will be conducted through Zoom for Healthcare and telephone contact between the peer counsellors and participants. Zoom sessions will be recorded for the purposes of supervision, which is intended for both clinical oversight and continued refinement of peer counsellor’s competencies and therapeutic skillset. In addition to between 6 and 8 structured BA therapy sessions, peer counsellors will also provide informal and unstructured peer support via telephone and/or text. This will include both participant-initiated and peer counsellor-initiated check-ins, sharing of information, and peer guidance. The peer support component will be available to participants up to 6 weeks postpartum, for a total possible length of time of 12 weeks. Peer counsellors may opt to be paired with subsequent participants following completion of the intervention and peer support components. All peer counsellors will receive weekly mandatory clinical supervision via 60-min remote group meetings provided by a clinical psychology graduate trainee, and additional individual supervision meetings as needed, to ensure patient safety and treatment fidelity, and peer counsellor adherence to the protocol. All trainee peer supervisors will be supervised by a registered clinical psychologist through regular virtual group supervision and one-on-one supervision as needed. Fidelity will be addressed with the weekly supervision sessions with the peer counsellors. During the weekly supervision sessions, it will be emphasized that external resources outside of what we provide them cannot be recommended. We will also request that peer counsellors keep an informal record of peer support that they deliver, which will be reviewed during supervision. Peer counsellors will be offered a stipend of $250 for each intervention cycle administered to a single participant, to acknowledge their time and contribution to the study. Following their final intervention cycle in the current study, peers will be invited to complete a qualitative individual in-depth interview, conducted by a trained research assistant under the supervision of the PIs ([name], [name]). Interviews will elicit reflective conversation around the experiences of peers in delivering the intervention, and any perceived positive or negative impacts the experience may have on their well-being. We will also explore their thoughts and opinions on strengths and weaknesses of the intervention and its delivery (including the training experience) and whether they have suggestions for improvement in the future.

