
The control group will receive standard of care, including receiving routine obstetric care and referral to community mental health resources, and will also complete all study assessments.

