## Assignment of interventions: allocation

### Sequence generation {16a}

Participants will be randomized using computer-generated blocked randomization (block size 4) in a 1:1 ratio to the intervention group or the control group. 123 participants will be randomized into each study group, with a total of 246 participants enrolled in the RCT.

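### Peer counsellors are shared by participants in the intervention arm only, and neither the named models nor the sample size allows for it; the likely effect is small

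*Protocol article*

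**What the plan says.** Protocol article, Sample size {14}: "A total of 60–75 peer counsellors will be recruited and trained", each of them "trained to provide the intervention to between 1 and 3 participants through the course of the study", with more recruited if needed. The same section states that "This sample size of 246 participants (123 per group) is adequate" to detect a 3-day difference in mean gestational age with 80% power. It also bases 90% power for a 25% difference in EPDS on a two-sided t-test with 214 participants, then adds 15% for attrition.

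Intervention description {11a}: a counsellor is paired with one participant at a time, and "Peer counsellors may opt to be paired with subsequent participants following completion of the intervention and peer support components". On the comparator: "The control group will receive standard of care, including receiving routine obstetric care and referral to community mental health resources". Controls therefore have no counsellor.

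Sequence generation {16a} sets the allocation: "Participants will be randomized using computer-generated blocked randomization (block size 4) in a 1:1 ratio to the intervention group or the control group". Randomization is of individuals, and counsellors are attached afterwards.

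Statistical methods {20a}: time-to-event analysis for gestational age, Cox or logistic regression to adjust for imbalance, and logistic regression for EPDS of 13 or more. Differences in the continuous EPDS and PROMIS scores "between intervention and control groups will be modelled using linear regression". No counsellor term, frailty or clustered variance is mentioned, but the section does not say that clustering will be ignored either.

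**The concern.** With 123 treated participants and 60–75 counsellors, the mean load is 123/75 = 1.64 to 123/60 = 2.05, so sharing a counsellor is part of the design. The counsellors are lay peers with four weeks of training. They deliver sessions adapted to the individual, plus unstructured support by text and telephone. Some variation in outcome between counsellors is therefore plausible.

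Such variation would correlate the outcomes of participants who share a counsellor, in one arm only. This is a partially nested design. Cox, logistic and linear regression with their usual model-based standard errors treat participants as independent. They would then make the intervention arm look more precise than it is. The error has one direction: any positive ICC gives intervals that are too narrow and a type I error above the nominal 5%.

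**Working it through.** **The plan's own figure.** 214 × 1.15 = 246.1, stated as 246 (123 per group). The attrition allowance is the whole of the step, so nothing in it covers clustering. The 80% and 90% power statements cannot be reproduced because no standard deviation is given; below they are taken as nominal values.

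**Inputs from the protocol.** 123 treated and 123 control participants; 60–75 counsellors; 1 to 3 participants each; controls as singletons.

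**Assumption.** The counsellor ICC is not given. It is varied from 0 to 0.10.

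**Effective cluster size**, m_eff = Σm² / Σm. The protocol does not fix how the load is spread, so the lowest and highest values that the 1-to-3 limit allows are used:
- 75 counsellors, most even split (27 treat 1, 48 treat 2): (27 + 192)/123 = 219/123 = 1.78.
- 60 counsellors, most uneven split (28 treat 1, 1 treats 2, 31 treat 3): (28 + 4 + 279)/123 = 311/123 = 2.53.

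An intermediate case with 60 counsellors (18, 21 and 21 treating 1, 2 and 3) gives 291/123 = 2.37.

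**Formulas** (equal arms and equal total variance):
- Design effect in the intervention arm: DE = 1 + (m_eff − 1) × ICC.
- True over unadjusted standard error of the arm difference: r = √[(1 + DE)/2].
- True two-sided type I error of the unadjusted test: 2 × [1 − Φ(1.96/r)].
- Power of a test that uses the correct standard error, from a nominal 80%: Φ(2.80/r − 1.96).
- Total N that restores nominal power: 246 × (1 + DE)/2.

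**Results**, from m_eff 1.78 to 2.53:

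| ICC (assumed) | DE | r | Type I error | Power (nominal 80%) | N needed |
|---|---|---|---|---|---|
| 0 | 1 | 1 | 5% | 80% | 246 |
| 0.01 | 1.008–1.015 | 1.002–1.004 | 5.04–5.09% | 79.7–79.9% | 247–248 |
| 0.05 | 1.039–1.076 | 1.010–1.019 | 5.22–5.44% | 78.5–79.2% | 251–256 |
| 0.10 | 1.078–1.153 | 1.019–1.038 | 5.45–5.89% | 77.0–78.5% | 256–265 |

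Example, upper end at ICC 0.10: DE = 1 + 1.53 × 0.10 = 1.153; r = √(2.153/2) = 1.038; N = 246 × 1.0764 = 264.8, rounded up to 265, which is 19 more. At ICC 0.10 the nominal 90% power for EPDS becomes 87.8% to 88.9%.

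**Ceiling.** If only 41 counsellors each treated 3 participants (fewer than planned), m_eff is 3. ICC 0.10 then gives r = 1.049, type I error 6.2% and N = 271.

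The formula is for a difference in means. For the logistic and Cox models it is an approximation.

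**The case against.** The strongest objection is that this is a condensed article. It names model families and leaves the variance estimator unstated, and all three families can be fitted with clustered standard errors. A reader might infer that every model will treat participants as independent and that the standard errors are too small. The text supports neither as fact. The first is a reading of silence, and an analysis plan that is not shown may settle it. The second needs an ICC above 0, which the documents do not give. What remains is that the article fixes the sample size and allows for attrition only, and that it assigns a model to each outcome without providing for a design feature it describes itself.

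A second objection is size: at an ICC of 0.05 the test runs at about 5.2% to 5.4% instead of 5%. That is correct, and it is why the point is minor.

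Third, the primary outcome is gestational age from health records, which a counsellor can affect only indirectly. Standardised training, competency approval and weekly supervision also aim to reduce differences between counsellors, and intention-to-treat keeps participants who were never reached. This stands as well. Clustering is more plausible for EPDS and PROMIS, though the documents have no figures for either.

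A reader might also infer that a counsellor term would let the trial say whether benefit depends on who delivers the intervention. It would not. That question is not among the objectives, and with about two participants each the ICC would be estimated too poorly. For 61 counsellors with 2 participants each and a true ICC of 0.05, its standard error is √[2 × 0.95² × 1.05² / (2 × 1 × 60)] = 0.129, more than twice the ICC itself.

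**Conclusion.** The concern holds in a limited, conditional form. Counsellor sharing is built into one arm, and neither the stated models nor the sample size allows for it. The harm depends on outcomes varying by counsellor, and even then small clusters keep it slight for the planned 60–75 counsellors and ICCs up to 0.10, as the table shows. These figures rest on the assumed ICC range, equal variances in the two arms and the 1-to-3 load limit. They would not overturn a clear result but could matter for a borderline one. The sample size does not need to be reopened. Minor severity.

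**What to change.** Keep the counsellor ID for every intervention participant in the analysis file. The link should already exist, because under Implementation {16c} research assistants notify counsellors of their assigned participants.

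In Statistical methods {20a}, or in the analysis plan if it is not already there, specify standard errors clustered on counsellor, with each control as its own cluster, for the linear, logistic and Cox models. At minimum, do this for the EPDS and PROMIS outcomes, and as a sensitivity analysis for gestational age. Make no claim about how benefit varies between counsellors.

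The cost is one variable, a few lines of code and slightly wider confidence intervals. No extra participants or assessments are needed.
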